### Research questions

The primary research question for family caregivers is:

Does iSupport improve family caregivers’ overall knowledge about dementia?

The secondary research questions for family caregivers are:

Does iSupport improve family caregivers’ caregiving skills required to care for PWD?Does iSupport reduce family caregivers’ stress?Does iSupport improve family caregivers’ mental health?Does iSupport improve family caregivers’ quality of life?Does iSupport improve family caregivers’ relationship with PWD?

The primary research question for formal caregivers is:

Does iSupport improve formal caregivers’ overall knowledge about dementia?

Secondary research questions for formal caregivers are:

Does the impact of iSupport on knowledge about dementia differ between male and female formal caregivers?Does the impact of iSupport on knowledge about dementia vary with the level of caregiving skills of formal caregivers?

In addition, this study aims to capture caregivers’ experience of using iSupport in relation to providing care for PWD, the perceived benefits and challenges of using iSupport, and recommendations for improving the iSupport intervention through qualitative methods.

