### Sample size

The primary objective of this study is to assess the effectiveness of the adapted iSupport manual in enhancing the overall knowledge about dementia and dementia care among both family and formal caregivers. The required sample size estimation was, thus, based on the DKAS. The DKAS has previously been used in multiple studies to assess knowledge and awareness of dementia especially among caregivers of PWD [39,48–50].

A hypothesis test on the mean difference between the pre- and post-intervention DKAS scores will be performed. The hypotheses of interest are as follows:

$$H_{0}:\mu_{d}=0$$

$$H_{1}:\mu_{d}\neq 0$$

where, *μ*_*d*_ is the mean difference of DKAS scores in the population. The sample size was estimated using the following formula:

$$\begin{array}{c} n={\left(\frac{Z_{1-\alpha /2}+Z_{1-\beta }}{\mu_{d}/\sigma_{d}}\right)}^{2} \end{array}$$

here, σd is the standard deviation of mean differences of DKAS scores in the population, $Z_{1-\alpha /2}$ is the value from the standard normal distribution at the significance level α, and $Z_{1-\beta }$ is the value at the power β.

According to a 2016 study by Annear and colleagues (2017) which validated the DKAS among an international cohort of participants, the mean DKAS score was about 34.5 (in a scale of 50; SD_Family_ = 6.8 and SD_Formal_ = 8.4) for both family and formal caregivers [39]. To estimate the sample size, relevant literature that used the DKAS to evaluate knowledge-based interventions related to dementia were consulted. Eccleston and colleagues (2019) evaluated the impact of participating in a Massive Open Online Course (MOOC) on dementia in improving knowledge related to dementia [48]. The course was offered world-wide, however, the majority of the participants (i.e., 74.3%) were from Australia. Their study used DKAS as an outcome indicator as in the proposed study. The published dataset was used to estimate the baseline and end-line DKAS scores [48]. According to the study, the mean difference between overall pre- and post-intervention knowledge scores was about 9.9 (SD = 8.7) and the mean score difference among the participants with exposure to dementia from their family was about 15.0 (SD = 9.0) [48].

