Using these estimates, the sample size was calculated according to the hypotheses of interest at 5% level of significance and 80% power of the test. Since majority of the data represent Australian population, the standard deviation of the mean differences was inflated while estimating the sample sizes. The standard deviation of the mean differences ($\sigma_{d}$) for the family caregivers was multiplied by a factor of three and $\sigma_{d}$ for formal caregivers was multiplied by a factor of two. This conservative approach is expected to help the knowledge assessment adjust for higher variation in DKAS scores. Moreover, the $\sigma_{d}$ for family caregivers was inflated by a higher factor because the family caregivers’ DKAS scores are expected to vary more than that of the formal caregivers. Using the formula, the estimated sample size was 26 for both family and formal caregivers. A 40% attrition rate was assumed since dropouts are comparatively high in these interventions [51]. Incorporating for the attrition, the adjusted sample size for this study would be 44.

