However, to test whether the impact of the iSupport manual on knowledge about dementia varies based on gender and caregiving skills a larger sample will be required. To test the knowledge related outcome between male and female formal caregivers, a sample size of 88 (i.e., 44 from each of the gender categories) will be required. The formal caregivers are categorised into three levels by their employer: Level 1, Level 2 and Level 3 (i.e., basic-, general-, and advance-care respectively). This classification is based on their practical skills, work ethics, and educational qualifications, with a minimum requirement of a Secondary School Certificate (10 years of schooling). The categorization of formal caregivers are indicators of their skills. Hence, to test whether the outcome varies among these three levels, a sample size of 132 (44 from each level) will be required. Moreover, the large sample size will allow potential differences in dementia knowledge between male and female formal caregivers before and after the intervention to be identified, as well as to explore whether baseline knowledge differs between the two groups. Therefore, a purposive sampling technique will be applied, and all the available formal caregivers from the specific agency offering formal caregiving services will be invited to participate in the survey. Family caregivers will also be purposively selected since there is no identified pool of family caregivers to create a sampling frame.

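### The 88 and 132 formal-caregiver totals multiply a within-group pre-post sample size, so they do not size the between-group tests by gender and skill level that they are said to serve

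*Protocol article*

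**What the plan says.** In the protocol article, Research questions lists two secondary questions for formal caregivers. One is "Does the impact of iSupport on knowledge about dementia differ between male and female formal caregivers"; the other asks the same across levels of caregiving skill. Both concern a difference in change between groups.

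The Sample size section sets up one hypothesis only: "A hypothesis test on the mean difference between the pre- and post-intervention DKAS scores will be performed", with a null of zero mean difference and a two-sided alternative. The formula is the paired, single-group one, applied "at 5% level of significance and 80% power of the test". It gives 26, which becomes 44 after 40% attrition.

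The section then says that more participants are needed to test whether impact varies by gender and skill. For gender, "a sample size of 88 (i.e., 44 from each of the gender categories) will be required". For the employer's three skill levels, "to test whether the outcome varies among these three levels, a sample size of 132 (44 from each level) will be required". The section gives no between-group hypothesis, no target difference in change and no two-group or three-group formula.

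**The concern.** The calculation answers one question and is cited for another. Forty-four per stratum is what the plan needs to show that knowledge changed among men, among women, or within one level. Whether the change differs between men and women is a separate hypothesis. With equal group sizes, the estimated difference between two mean changes has twice the variance of one mean change. The difference of interest is also usually smaller than the change itself.

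These are the only secondary questions for formal caregivers, and they are the stated reason for raising the formal sample from 44 to 132. If the rationale stands, the study appears to be sized for subgroup comparisons whose power was never worked out.

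**Working it through.** **Inputs (protocol article, Sample size).** Two-sided alpha 0.05 and power 0.80, so z₀.₉₇₅ + z₀.₈₀ = 2.802. Mean change and SD: 9.9 and 8.7 overall; 15.0 and 9.0 for those exposed to dementia through family. SD multipliers: two for formal caregivers (2 × 8.7 = 17.4) and three for family caregivers (3 × 9.0 = 27.0). Attrition 40%. The section does not say outright that 9.9 and 8.7 belong to formal caregivers. I infer it, because that pair with the factor of two comes close to the stated 26.

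**The plan's own figures**, n = (2.802 × σ_d / μ_d)²:
- Family: (2.802 × 27.0 / 15.0)² = 25.4, so 26.
- Formal: (2.802 × 17.4 / 9.9)² = 24.2, so 25; stated as 26.
- Attrition: 26 / 0.60 = 43.3, so 44.
- 2 × 44 = 88 and 3 × 44 = 132.

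The arithmetic reproduces, and both totals are exact multiples of the one-group size.

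**What those numbers give for a between-group difference.** The plan states no target, so I assume two: 9.9 points (as large as the whole expected change) and 4.95 (half of it). Completers are 26 per group (44 less 40%), or 0.60 × 132 ≈ 79 in all. Gender uses the two-sample t-test on change scores (noncentral t), with standard error SD × √(1/n₁ + 1/n₂). For example, 17.4 × √(2/26) = 4.83. Levels use the one-way F-test (noncentral F). Each range in the level rows covers evenly spaced means and one level apart from two equal ones.

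| Comparison | Completers | SD | Power, 9.9 | Power, 4.95 | Detectable at 80% |
|---|---|---|---|---|---|
| Gender | 26 v 26 | 17.4 | 52% | 17% | 13.8 |
| Gender | 39 v 40 | 17.4 | 70% | 24% | 11.1 |
| Gender | 26 v 53 | 17.4 | 65% | 22% | 11.8 |
| Three levels | 26 each | 17.4 | 42–54% | 13–16% | range 13.2–15.3 |
| Gender | 26 v 26 | 8.7 | 98% | 52% | 6.9 |
| Gender | 39 v 40 | 8.7 | 99.9% | 70% | 5.6 |
| Gender | 26 v 53 | 8.7 | 99.7% | 65% | 5.9 |
| Three levels | 26 each | 8.7 | 96–99% | 42–54% | range 6.6–7.6 |

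**The plan's formula carried over to two groups**, n per group = 2 × (2.802 × SD / difference)², at SD 17.4:
- 9.9 points: 48.5, so 49 completers and 82 recruited per gender.
- 4.95 points: 194 completers and 324 recruited per gender.

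**The case against.** The strongest reply is that the sample is not shown to be too small. A reader might infer that neither 88 nor 132 can answer the subgroup questions. The document does not support that, because it fixes neither a between-group target nor an SD for this comparison. At the source SD of 8.7, a 9.9-point difference has 98% power for gender with 26 per group and 96–99% across three levels. This stands: insufficiency is conditional. It does not rescue the rationale, since the plan chose 17.4 as its cautious basis and names no target at either SD.

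It is also fair that the operative target is 132, not 88. The gender comparison should therefore be judged on about 79 completers, which lowers its detectable difference from 13.8 to about 11–12 points at SD 17.4.

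Three further inferences are tempting but not supported:
- That gender and skill will be handled only as confounders. The Data analysis plan also promises regression of outcomes on background variables, and how an effect-modifier term is coded belongs to an analysis plan.
- That the agency cannot supply 44 per stratum. Its staff numbers by gender and level are not given, so no shortfall is shown.
- That the authors will read a null comparison as equal benefit. Nothing in the article says so.

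Finally, these are secondary questions in a non-randomised feasibility study. The primary pre-post test among formal caregivers is not weakened, since 132 exceeds the 44 it needs.

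**Conclusion.** The point holds as a mismatch between the stated sample size and the hypothesis it is cited for; it is not an arithmetic slip. Forty-four per stratum gives about 80% power for change within a stratum. The statement that 88 and 132 are required for the between-group tests has no basis in the calculation shown.

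On the plan's own inflated SD, a gender difference as large as the entire expected effect would be detected with at most about 70% power, and a three-level spread of that size with 42–54%. At half that difference, power is 24% or less. On the uninflated SD, large differences are well covered, while 4.95 points has about 42–70% power.

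These figures rest on the assumed differences of 9.9 and 4.95, on assigning 9.9 and 8.7 to formal caregivers, on 40% attrition falling evenly, on a common SD across groups, and on unadjusted change scores.

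**What to change.** Keep 132 and reword the Sample size section:
- State that 44 per stratum powers the pre-post change within that stratum only.
- Label the gender and skill-level comparisons exploratory.
- State their detectable differences at 80% power. For gender with about 79 completers: about 11–12 points at SD 17.4 and 5.6–5.9 at SD 8.7. For three levels with 26 completers each: a range of means of about 13–15 points and 7–8 points respectively.
- Say that these questions will be answered by the between-group difference in DKAS change with its 95% CI, not by setting separate within-group paired t-tests side by side.

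The difference in change should come first, because it is what the research questions ask. Gender and employer-assigned level are pre-existing groups that may differ at baseline, so a baseline-adjusted contrast can answer a different question; it may be added as a sensitivity analysis.

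The cost is wording and one pre-stated comparison, with no extra participants. The downside is a weaker claim for the two secondary questions. The alternative is to state a between-group target and size for it, which at SD 17.4 means 164 recruited (2 × 82) for a 9.9-point gender difference and 648 (2 × 324) for 4.95.

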### Data collection plan

Once the iSupport manual has been fully translated, reviewed, and face-validated through stakeholder workshops, participant recruitment and data collection will commence. Trained data collectors will conduct the data collection. The data collectors will undergo vigorous training on the study instruments prior to data collection. Data collection will begin with a baseline survey, after which participants will gain access to the manual for two months. At the end of the two months, an end-line survey will be conducted. Following the end-line survey, qualitative interviews to explore the experiences, facilitators, and barriers of using iSupport will be conducted. Finally, a follow-up survey will be conducted to test the retention of knowledge on dementia after three months of the end-line survey. Figs 1 and 2 show the adaptation, participant recruitment and data collection timeline of family and formal caregivers.

The DKAS [39] will be used at baseline and end-line to assess the primary objective for both family and formal caregivers. The DKAS will also be used three months after the end-line to assess the retention of knowledge among both caregiver groups. The CC, MCSI [40], CES-D-10 [41], GAD-7 [42], CarerQoL [43] and QCPR [44] will be administered at baseline and end-line only to assess the secondary objectives relating to family caregivers in this study. All data collection tools used will be used to record caregivers’ responses only and will not involve the PWD. The timeline for administering each tool is shown in Fig 4.

**Fig 4 pone.0326207.g004:**
[figure not shown]
Data collection and tool administration timeline.

In addition, baseline data such as gender, age, participants’ socio-demographic, economic features, and experience of caregiving will be collected. Website analytics will be collected to assess participants’ adherence to the program. Combined with website analytics, a self-reported adherence module at end-line will be used to assess adherence. Moreover, a minimum of 15 individual qualitative interviews with family caregivers and four FGDs with formal caregivers will be conducted after the end-line. Additional interviews and FGDs may need to be conducted until data saturation is reached. Participants with varied degrees of adherence will be invited to participate in the interviews and FGDs.

### Data management

A meticulous data management and monitoring plan will be followed. Data will be collected primarily on SurveyCTO, a secure mobile data collection platform. The datasets generated will be uploaded and securely stored on a password-protected secure server to safeguard unauthorized access. Audio-recordings from qualitative interviews will be deleted from the recording device after they have been copied to a password-protected secure storage device. Moreover, website analytics along with participants’ emails used to sign up on the website will be stored.

Hard copies of the consent forms by the study participants will be safely stored in locked and fireproof filing cabinets. Digitized versions of the consent forms will also be stored on a password protected cloud. Study participants will each be pseudonymized with a unique identification number in the database. This unique identification number will be used to facilitate data linkage throughout the study. Only authorized members of the research team will have access to the datasets. De -identified participant data will be made publicly available as supplementary information, accompanying the publication of results, in accordance with ethical guidelines and data protection regulations.

To ensure data accuracy, a rigorous quality assurance process will be implemented. Initial data entry will be cross-checked by a member of the research team, with periodic random data entry checks after. The research team will also conduct weekly meetings to monitor data collection activities and ensure adherence to protocols.

### Data analysis plan

The quantitative results of pre- and post-intervention assessments will be compared. It is hypothesised that statistically significant differences between the pre- and post- outcome indicators will be found. The null hypothesis of zero mean difference will be tested using a two-sample paired t-test for all the outcome indicators. Moreover, multivariable statistical techniques will also be used to control for possible confounders (e.g., gender, age, caregiving skills). Moreover, descriptive and regression analyses will be conducted to identify associations between background and outcome variables. In case of missing data, simple imputation methods will be used. For continuous variables, missing values will be replaced with the mean, while for categorical variables, the mode will be used.

To analyse the qualitative data, content analysis with an inductive approach will be used. The qualitative interviews and FGD recordings will first be transcribed verbatim, ensuring accuracy and completeness. The transcripts will then be translated to English as all interviews will be conducted in the participants’ native language, Bangla. The transcripts will be thoroughly read to identify meaning units, codes, and categories [52]. The process of inductive content analysis includes open coding, creating subcategories, and abstraction to categories. Findings will be discussed back and forth among the authors until they reach a consensus, to increase validity. Transferability will be ensured through a detailed description of the data collection process and a sensitivity to the context in which data will be collected. No software will be used for data analysis.

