## Abstract

Dementia is a growing global public health concern, particularly in LMICs like Bangladesh. With population aging, there is an increasing prevalence of dementia; care facilities are limited. This scarcity of services places a significant responsibility on untrained family caregivers, impacting the health of persons with dementia and their caregivers. Addressing these challenges is crucial for improving dementia care, especially in resource-constrained settings. Recognizing the urgency, the WHO developed an online self-training manual, iSupport, emphasizing education, skill development, and support for caregivers. This study aims to test feasibility of iSupport i) in improving knowledge about dementia and dementia care among family and formal caregivers, and ii) reducing family caregivers’ stress and improving their caregiving skills, mental health, quality of life and relationship with the person with dementia cared for. The study protocol was approved by the Institutional Review Board of SAJIDA Foundation (2024–005-SFIRB). This non-randomized feasibility study aims to recruit 44 family caregivers and 132 formal caregivers from Dhaka, Bangladesh, using a purposive sampling technique. Participants will be provided access to iSupport for two months. Pre- and post-intervention surveys will be conducted to assess changes in knowledge about dementia care among both family and formal caregivers, as well as changes in psychological well-being among family caregivers. To assess knowledge retention, a follow-up survey will be conducted. Any differences in the outcomes from the pre-intervention period will be tested against the null hypothesis of zero mean difference using a two-sample paired t-test. Additionally, multivariable regression techniques will also be used to control for possible confounders. To understand the facilitators and barriers of implementing iSupport, a qualitative approach will be used to interview 15 family caregivers and conduct four FGDs with formal caregivers. Qualitative data will be analysed using an inductive content analysis approach.

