## Materials and methods

### Study design

This is a non-randomized study assessing the feasibility of the iSupport manual for family caregivers of PWD and formal caregivers in Dhaka, Bangladesh. A quantitative approach will be used to answer the research questions. Quantitative data will be collected at pre- and post-intervention surveys to assess changes in knowledge about dementia care among both family and formal caregivers, as well as changes in psychological well-being among family caregivers. To assess knowledge retention, a follow-up survey will be conducted three months after the post-intervention survey. Moreover, individual qualitative interviews and Focus Group Discussions (FGDs) will be conducted with caregivers after the intervention period to gain understanding of their experiences of using iSupport and possible facilitators and barriers related to using iSupport. The intervention and data collection phases for this study is expected to take around 10 months. This study protocol adheres to the SPIRIT (2013) checklist (S1 File).

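### The three-month DKAS is meant to test knowledge retention, but the only stated test is against zero change from baseline, which does not show whether the end-line gain was kept

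*Protocol article*

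**What the plan says.** Retention is given as the purpose of the third survey in three sections of the protocol article. The Abstract states: "To assess knowledge retention, a follow-up survey will be conducted". Study design repeats this and fixes the timing at three months after the post-intervention survey. The Data collection plan uses the word test: "a follow-up survey will be conducted to test the retention of knowledge on dementia after three months of the end-line survey". It also names the instrument and the groups: "The DKAS will also be used three months after the end-line to assess the retention of knowledge among both caregiver groups".

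The analysis text does not follow this through. The Data analysis plan opens with "The quantitative results of pre- and post-intervention assessments will be compared" and continues: "The null hypothesis of zero mean difference will be tested using a two-sample paired t-test for all the outcome indicators". It does not mention the follow-up survey. The Abstract, directly after its sentence on retention, gives the reference point: "Any differences in the outcomes from the pre-intervention period will be tested against the null hypothesis of zero mean difference". The Sample size section plans only for the pre-post change in DKAS.

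Nowhere does the article name an end-line to follow-up contrast, define retained knowledge, or give a margin.

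**The concern.** Retention is a statement about end-line versus follow-up: how much of what was gained is still there three months later. The stated null is zero change, and the only stated reference is baseline. A follow-up mean can lie clearly above baseline when most of the gain has gone, so a significant result does not separate kept knowledge from largely lost knowledge.

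Moving the same zero-difference test to follow-up minus end-line would put the right two surveys together but leave a second problem. The result that favours retention would then be a non-significant one, and in a small or variable group that may reflect imprecision only.

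The Discussion plans to take the findings to care providers and policy briefings, and sees them as groundwork for scale-up. A statement that knowledge lasted would carry weight there, so the contrast behind it should be fixed in advance.

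**Working it through.** **Inputs, all from the Sample size section.** The planning gain is 15.0 points (SD 9.0) for family caregivers. The overall gain of 9.9 points (SD 8.7) is taken as the formal caregiver input. The SDs are inflated by 3 for family (27.0) and by 2 for formal caregivers (17.4). Alpha is 5% two-sided, power 80%, attrition 40%. Recruitment targets are 44 family and 132 formal caregivers.

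**The plan's own figure.** n = ((z₀.₉₇₅ + z₀.₈₀) × σ_d / μ_d)², with (1.960 + 0.842)² = 7.849.
- Family: 7.849 × (27/15)² = 25.43, rounded up to 26.
- Formal: 7.849 × (17.4/9.9)² = 24.25, rounded up to 25. The article gives 26 for both groups.
- Attrition: 26 / 0.6 = 43.3, rounded up to 44.

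The stated 26 and 44 are reproduced, and they concern the pre-post contrast only.

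**Assumptions for the check.** Completers at follow-up are 60% of those recruited: 44 × 0.6 = 26.4, so 26 family; 132 × 0.6 = 79.2, so 79 formal. The planning gains are reached at end-line. The SD of the change to follow-up is not given, so it is ranged from the published to the inflated pre-post value.

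**Test against baseline.** The smallest observed mean change that is significant is t(0.975, n−1) × SD / √n. Dividing by the planning gain gives the share that must remain.

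| Group | n | SD | Smallest significant change | Share of gain that must remain | Share that may be lost |
|---|---|---|---|---|---|
| Formal | 79 | 8.7 | 1.991 × 8.7/√79 = 1.95 | 1.95/9.9 = 20% | 80% |
| Formal | 79 | 17.4 | 1.991 × 17.4/√79 = 3.90 | 3.90/9.9 = 39% | 61% |
| Family | 26 | 9 | 2.060 × 9/√26 = 3.64 | 3.64/15 = 24% | 76% |
| Family | 26 | 27 | 2.060 × 27/√26 = 10.91 | 10.91/15 = 73% | 27% |

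If only 40% of the gain is truly kept, the noncentral t gives these chances of a significant result against baseline: formal 98% (SD 8.7) and 52% (SD 17.4); family 90% (SD 9) and 19% (SD 27).

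**Test against end-line.** Power to detect a true loss of half the gain, again from the noncentral t: formal more than 99% (SD 8.7) and 70% (SD 17.4); family 98% (SD 9) and 28% (SD 27). In the last case a loss of half the gain would be non-significant about 73% of the time.

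**The case against.** The strongest reply is that this is a gap, not an error. The Data analysis plan covers the pre-post comparison, which matches the primary research questions and the hypotheses in the Sample size section. The contrast for an extra time point is something that a journal article may leave to a fuller document. The Abstract sentence speaks of outcomes in general, most of which are collected only at baseline and end-line, so it may simply summarise the pre-post test. Retention appears in neither the Objectives nor the Research questions.

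Much of this stands, and it limits the point. What remains is that the article commits to testing retention and states one reference point and one null, and these do not answer that question. Carrying them over faithfully into an analysis plan would not repair the mismatch.

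Three stronger readings are tempting, and the documents do not support them.
- A reader might infer that the study will declare knowledge retained whenever follow-up exceeds baseline. The article never says so. This is only what the stated test would yield if it were used for that purpose.
- A reader might infer that the study cannot answer its retention question. It can: DKAS is collected at all three surveys in both groups, and Data management provides for linkage by a unique identifier.
- A reader might infer that a non-significant decline from end-line is likely whatever the truth. For a loss of half the gain, that fails in three of the four scenarios above. Power is low only for family caregivers at SD 27, which is a deliberate planning inflation.

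**Conclusion.** The concern holds in a limited form. As stated, the test does not measure retention, and its result against baseline is compatible with a large loss of the gain: 61% to 80% for formal caregivers across the SD range, and up to 76% for family caregivers at the published SD. It is not misleading in this direction for family caregivers at SD 27. There the weakness moves to the other reading, because a non-significant decline from end-line would be poor evidence of retention.

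The percentages depend on 60% completers, on the planning gains being reached, and on the SD of the follow-up change lying between the published and inflated pre-post values. The documents give no figure for that SD. The mismatch of reference point and question does not depend on these numbers. The primary pre-post analysis is unaffected.

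**What to change.** In the Data analysis plan, and to match in the Abstract:
- State that retention is assessed by mean DKAS at follow-up minus end-line, with a 95% CI, separately for family and formal caregivers.
- Keep follow-up minus baseline as a supporting contrast, and report the share of the baseline to end-line gain that is kept as a descriptive figure.
- State that neither significance against baseline nor a non-significant decline from end-line will by itself be called retention.

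A formal retention margin is optional. If one is used, it should be a fixed number of DKAS points set before data collection. A fraction of the observed gain is not pre-set, since it depends on the data, and a simple CI for the decline would ignore the uncertainty in that gain.

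The cost is some wording and one further contrast on data already planned. The downside is precision. If the SD range above also applies to this contrast, the 95% CI half-width is about 1.95 to 3.90 points for formal caregivers and 3.64 to 10.91 points for family caregivers, so the family result may support no firm statement either way.
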